**CONFIDENTIAL**

## Protocol Synopsis

### I . Protocol title:

A Phase I, Randomized, Open-Label Study to Evaluate the Safety and Immunogenicity of EV71 Vaccine Administrated with Adjuvant AIPO4 in Health Volunteers

### II . Objectives:

Enteroviruses (EV) are small RNA (ribonucleic acid) viruses associated with several human and mammalian diseases. It can cause outbreaks of hand-foot-and-mouth disease (HFMD) or herpangina, and is sometimes associated with severe neurologic complications. Several enterovirus epidemics have been reported in Taiwan, and enterovirus 71 (EV-71) infection was associated with most of the serious clinical manifestations.

This study aims to evaluate the safety, reactogenicity and immunogenicity of EV71 vaccine at a 5-µg and 10-µg dose in health volunteers

#### 1. Pimary objective:

- ◆ To evaluate the safety and reactogenicity of the EV71 vaccine at a 5-µg and 10-µg dose.

#### 2. Secondary objective:

- (1) To evaluate the immunogenicity in terms of immunoglobulin G (IgG) titers induced by the EV71 vaccine at a 5-µg and 10-µg dose.
- (2) To evaluate the immunogenicity in terms of neutralizing antibody titers from baseline induced by the EV71 vaccine at a 5-µg and 10-µg dose.
- (3) To identify the immunodominant epitopes of EV71 virus by human serum.

### III . Test vaccine:

#### 1. Name: EV71 Vaccine

#### 2. Dosage form: Injection, 3 ml sterile suspension/vial (applied for maximum 5 doses at the same time), 20 µg/ml viral protein with adjuvant 600 µg/ml aluminium (AIPO4)

#### 3. Dose:

- (1) Group A05: 0.25 ml per dose (5 µg total protein + adjuvant 150 µg AIPO4)
- (2) Group B10: 0.5 ml per dose (10 µg total protein + adjuvant 300 µg AIPO4)

#### 4. Dosing schedule: Two intramuscular (i.m.) vaccinations, 21 days apart (on Day 0 and Day 21)

#### 5. Mechanism of action: Preventive vaccination of inactivated EV71 whole virion (EV71vac bulk) to induce antibody against EV71 virus.

#### 6. Pharmacological category: Vaccine

### IV . Developmental phase: phase ☒ I ☐ II ☐ III (☐ III a or ☐ III b) ☐ IV ☐ Others

### V . Study design:

1. ☐ Control: ☐ placebo  
☐ active \_\_\_\_\_  
☐ other \_\_\_\_\_
- ☒ Uncontrolled
2. Blinding: ☒ open-label ☐ evaluator blind ☐ single blind ☐ double blind  
☐ double dummy ☐ other \_\_\_\_\_
3. Randomized: ☒ yes ☐ no
4. ☒ Parallel ☐ Cross-over ☐ Other \_\_\_\_\_
5. Duration of treatment: Two-vaccination regimen, 21 days apart
6. Titration: ☐ forced ☐ optional ☒ none
7. ☐ Multi-national ☒ Multi-center (Taiwan) ☐ Single center

## VI. Endpoints

1. Primary endpoint:
- ◆ The percentage, intensity and relationship to vaccination of local and systemic signs and symptoms at a 5-µg and 10-µg dose under the following time frames:
    - Solicited adverse events: during 7-day follow-up period
    - Unsolicited adverse events: during 21-day follow-up period
  - ◆ The occurrence of overall adverse events and serious adverse event at a 5-µg and 10-µg dose during the entire study period.
2. Secondary endpoints:
- (1) Observed variables from baseline at a 5-µg and 10-µg dose on Day 21 and 42:
- Serum IgG titers
  - Serum neutralizing antibody titers
  - Epitope mapping (only on Day 42)
- (2) The change in the laboratory results:
- Hematology
  - Biochemistry

## VII. Selection criteria:

1. Main inclusion criteria:
- (1) Female and male  $\geq 20$  and  $\leq 60$  years of age at the time of first vaccination.
  - (2) Subject who is free of obvious health problems as established by medical history and physical examination based on the investigator's clinical judgment.
  - (3) Able and willing to comply with the study procedure and give written informed consent.
2. Main exclusion criteria:

- (1) Female who is pregnant/lactating or planning to be pregnant, or female of childbearing potential\* who is not using medically recognized method of contraception\*\*.

\* Other than those who have been surgically sterilized (defined as having undergone hysterectomy or bilateral oophorectomy or bilateral salpingectomy; tubal ligation alone is not considered sufficient) or one year post-menopausal.

\*\* Recognized contraceptive precautions, including intrauterine contraceptive device; oral contraceptives; diaphragm or condom in combination with contraceptive jelly, cream or foam; Norplant® or DepoProvera®, should be conducted until 2 months after completion of the vaccination series.

- (2) Subject with body mass index (BMI) > 35.
- (3) Subject with fever defined as oral temperature  $\geq 37.5^{\circ}\text{C}$  at the time of planned vaccination.
- (4) Subject with previous known or potential exposure to Enterovirus 71 (EV71).
- (5) Subject with a history of herpangina, hand-foot-mouth disease, acute hemorrhagic conjunctivitis or acute gastrointestinal illness associated with enterovirus infection in the past 3 months.
- (6) Subject with any confirmed or suspected abnormal immune function, immunosuppressive or immunodeficient condition.
- (7) Subject who has been diagnosed with a significant neurological, pulmonary, cardiovascular, hematological, hepatic or renal disorder.
- (8) Subject with any abnormal laboratory results at screening.
- (9) Subject with a history of hypersensitivity to vaccines, or a history of allergic disease or reactions likely to be exacerbated by any component of the vaccine.
- (10) Use of any investigational/non-registered product (including drug, vaccine and invasive medical device) within 30 days prior to vaccination or planned use during the study period.
- (11) Administration of any licensed vaccine within 30 days prior to vaccination or planned administration during study period (until 30 days after the second vaccination).
- (12) Use of immunoglobulins or any blood products within 3 months prior to vaccination or planned use during the study period (until 30 days after the second vaccination).
- (13) Chronic administration (defined as > 14 days) of immunosuppressants or other immunomodulators within 6 months prior to vaccination or planned use during the study period (until 30 days after the second vaccination).

\* For corticosteroids, this includes prednisone  $\geq 0.5$  mg/kg/day or equivalent. Inhaled and topical steroids are allowed.
- (14) Chronic or long-term (defined as > 14 days) use of acetylsalicylic acid medication within 6 months prior to vaccination or planned use during the study period (until 30 days after the second vaccination).
- (15) Known or suspected with alcohol or substance abuse.
- (16) Subject with any medical or psychiatric condition, including the presence of

significant laboratory abnormalities, which is a contraindication to protocol participation based on the judgment of the investigator.

**3. Treatment discontinuation:**

Withdrawal criteria:

- (1) Subject consent withdrawal.
- (2) Lost to follow-up.
- (3) Administration of prohibited medication/treatment/vaccine.
- (4) Any pathological event, clinical adverse event, or any change in the subject's status giving indication to the physicians that further participation in the study may not be the best interest of the subject.

Contraindications to second vaccination:

- (1) Subject with any abnormal laboratory results\* at safety screening visit (Visit 3).  
\* Subject with ALT/AST or creatinine > 1 x ULN but < 2.5 x ULN could be re-tested 1 week later.
- (2) Pregnancy
- (3) Subject with fever defined as oral temperature  $\geq 37.5^{\circ}\text{C}$  at the time before second vaccination.
- (4) Subject with acute disease at the time before the second vaccination (defined as the presence of a moderate or severe illness with or without fever).

**VIII. Study procedures:**

This is a phase I, prospective, randomized, open-label, two-center study. 60 eligible healthy volunteer will be recruited into this study. After enrollment, all subjects will be randomized to 2 dosing groups, Group A05 or Group B10, in a 1:1 ratio. Both groups will follow the same visit structure and be administrated 2 doses of EV71 vaccine under the dosage below on Day 0 and Day 21, respectively.

- ◆ **Group A05:** 0.25 ml per dose (5  $\mu\text{g}$  total protein + adjuvant 150  $\mu\text{g}$   $\text{AlPO}_4$ )
- ◆ **Group B10:** 0.5 ml per dose (10  $\mu\text{g}$  total protein + adjuvant 300  $\mu\text{g}$   $\text{AlPO}_4$ )

The study recruitment should be carried out in 2 parts, Part I and Part II.

**Part I:** This part of study will be conducted in one center. It will consist of the first 10 subjects who will have sequential enrollment. Following a blocking factor of safety, these subjects will be recruited in 3 blocks, Block A, Block B and Block C.

- ◆ Block A: Only the first subject will be assigned to Block A. He/she will be vaccinated with EV 71 vaccine 0.25 ml (5  $\mu\text{g}$  total protein with adjuvant 150  $\mu\text{g}$   $\text{AlPO}_4$ ).
- ◆ Block B: Block B will be initiated 7 days safety monitoring after the first vaccination of Block A. There will be 2 subjects recruited into this block at the same time, and they will be randomized into two dosing groups, Group A05 and Group B10, respectively.
- ◆ Block C: Block C will be initiated 7 days safety monitoring after the second vaccination of Block B and 7 subjects will be enrolled into this block at the same time. Three of them will be randomly assigned to Group A05 and the other 4

subjects will be randomly assigned to Group B10.

**Part II:** This part of study will be conducted in two centers. It will consist of the rest 50 subjects and should be initiated after the DSMB (Data and Safety Monitoring Board) evaluation conducted 14 days after the second vaccination of Block C.

All subjects should complete at least 7 visits, including the last 2 telephone visits. Additional visit, Visit 2a (Day 3) and Visit 4a (Day 24) will be conducted first in Part I for monitoring creatine kinase (CPK) in subjects at the third day after 1st and 2nd vaccination. Whether these 2 visits will be performed again in Part II depended on the DSMB's professional judgments. The immune response, including serum IgG and neutralizing antibody titers, will be assessed at Visit 2, 4 and 5 (baseline, Day 21 and Day 42), and immune epitope mapping of EV71vac will be conducted at Visit 2 and Visit 5. A post-vaccination diary card will be dispensed for the solicited/unsolicited symptoms, and a telephone follow-up will be conducted 7 days after each vaccination and/or 14 days after second vaccination (only for subjects in Block C). The safety of EV71 vaccine will be monitored throughout the whole study period.

The investigator team (Principal Investigator and Co-Investigators) should, on an ongoing basis, review the subject's safety data (including all AE recorded on the diary card and detected during study period) immediately and make medical judgment whether the adverse event is vaccine-related or not. The independent DSMB should monitor all the safety data as well. The second part of study could be conducted only when there is no safety concerns regarding the EV71 vaccine (evaluated on 14 days after the second vaccination of Block C). Moreover, the study recruitment should be suspended if any of the following criteria is met.

- (1) Any subject with severe local reaction, including ulceration, abscess or necrosis.
- (2) Any subject develops laryngospasm, bronchospasm or anaphylaxis.
- (3) Two or more subjects develop severe urticaria.
- (4) Any vaccine-related SAE during study period.

All subjects will be asked to preserve the residue blood samples for further research through a separate question in informed consent.

#### **IX. Concomitant treatment:**

##### **1. Permitted:**

Any treatment other than those prohibited below may be administrated during this trial. All concomitant treatments except vitamins and dietary supplements should be recorded in the Case Report Form.

##### **2. Prohibited:**

- (1) The following treatments are prohibited until 30 days after the second vaccination:
  - Other vaccine
  - Immunoglobulins
  - Any blood products
  - Immunosuppressants or other immunomodulators\*

\* For corticosteroids, this includes prednisone  $\geq 0.5$  mg/kg/day or equivalent.

Inhaled and topical steroids are allowed.

- Chronic or long-term (defined as > 14 days) use of acetylsalicylic acid medication

(2) The following treatments are prohibited during the study period:

- Investigational/non-registered product (including drug, vaccine and invasive medical device)

#### X. Statistics:

1. Primary hypothesis: ☐superiority ☐non-inferiority  
☐equivalence ☒other NA

2. Sample size: 60

3. Efficacy population: ☐ITT ☐PP ☒other ATP

Safety population: ☐ITT ☐PP ☒other Who receives at least one vaccination

4. Statistical method(s) for safety/immunogenicity evaluations:

- (1) The major analysis will be performed according to The Total Vaccinated cohort (TVC), According-To-Protocol (ATP) cohort for analysis of immunogenicity and According-To-Protocol (ATP) cohort for analysis of safety.
- (2) For descriptive statistics, continuous variables will be presented as mean, standard deviation, median and range; Categorical variables will be presented in frequency table.
- (3) All adverse events will be coded through MedDRA system and provided by system of organ and preferred term. The analysis of subjects experienced adverse events/serious adverse events will consist of a standardized tabulation of counts, percentage and 95% confidence interval of all observed adverse events (solicited and unsolicited).
- (4) The mean change of immunogenicity parameters include serum IgG and neutralizing antibody titers from baseline will be presented descriptively and assessing by paired T-test or Wilcoxon signed rank test under significance level 0.05. The summary results of immune epitope mapping will be presented descriptively.
- (5) The mean change of laboratory parameters from baseline will be presented descriptively and assessing by paired T-test or Wilcoxon signed rank test under significance level 0.05.

5. Planned interim analysis: ☒yes ☐no

An interim safety analysis will be conducted 14 days after the second vaccination of Block C. The second part of study could be initiated only after the interim report has been reviewed and approved by DSMB.

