### 1.2. Study rationale

Currently there are no vaccines or effective anti-viral drugs for EV71 treatment or prophylaxis, only supportive care can be conducted in patients acquired with EV71. According to seroepidemiologic study, more than half of children in Taiwan have no resistance to EV71, it suggested that in the future large EV71 outbreaks for the second time in Taiwan is still a possibility. If there is no effective way to control EV71 distribution, this will make the whole society in a panic and stress condition, especially in families with small children. For this reason, development of new antiviral drugs or vaccine for EV71 is high priority for high prevalence countries or regions, and vaccination of children under 5

years of age may be warranted.

Taiwan Center of Disease Control (Taiwan CDC) has made significant research progress in the bioprocess for producing cell-cultured-based whole-virion EV71 candidate vaccine using the roller-bottle technology. To carry-on the development of a vaccine against EV71 infection, Vaccine Research and Development Center (VRDC) at National Health Research Institute has the basic technology through technology transfer agreement with Taiwan CDC. VRDC also initiates the project of Taiwan Human Vaccine R&D Programs funded by Department of Health (DOH).

After obtaining the virus strain and Vero cells from Taiwan CDC, VRDC has established working cell and working virus bank for ensuring the adequate supply of equivalent quality of starting materials. The preparation and production processes were conducted in cGMP facility of VRDC and serum-free production process was first adopted by VRDC for generating higher quality and safety of EV71 vaccine. As so far, preclinical study has been completed and the preliminary data showed that EV71vac is safe enough to elicit functional antibody in animal model.

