**Figure 3-1 Study subject enrollment process:**

[figure not shown]

The study recruitment should be carried out in 2 parts, Part I and Part II.

**Part I:** This part of study will be conducted in one center. It will consist of the first 10 subjects who will have sequential enrollment. Following a blocking factor of safety, these subjects will be recruited in 3 blocks, Block A, Block B and Block C.

- ◆ **Block A:** Only the first subject will be assigned to Block A. He/she will be vaccinated with EV 71 vaccine 0.25 ml (5 µg total protein with adjuvant 150 µg AlPO4).
- ◆ **Block B:** Block B will be initiated 7 days safety monitoring after the first vaccination of Block A. There will be 2 subjects recruited into this block at the same time, and they will be randomized into two dosing groups, Group A05 and Group B10, respectively.
- ◆ **Block C:** Block C will be initiated 7 days safety monitoring after the second vaccination of Block B and 7 subjects will be enrolled into this block at the same time. Three of them will be randomly assigned to Group A05 and the other 4 subjects will be randomly assigned to Group B10.

The investigator team (Principal Investigator and Co-Investigators) should, on an ongoing basis, review the subject's safety data, including all solicited/unsolicited symptoms recorded on the diary card and all AE detected during study period, immediately and make medical judgment whether the adverse event is vaccine-related or not. Block B and Block C will only be taken place after the investigator confirms the initial safety of prior block.

**Part II:** This part of study will be conducted in two centers. It will consist of the rest 50 subjects and should be initiated after the DSMB (Data and Safety Monitoring Board) evaluation conducted 14 days after the second vaccination of Block C. Subjects in this part will be randomized equally to Group A05 and Group B10.

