#### **7.2.2. Neutralizing antibody titers**

Determination of EV71 virus neutralization titer is to determine the virus neutralization titer against EV71 virus based on the principle of TCID50 assay. Serum specimens will be serially 2-fold diluted and added into each well of the 96-well plate. 100 TCID50 of EV71

virus (E59) will be added into each well. The 96-well plate will be incubated at  $37\pm0.5^{\circ}\text{C}$  supplied with 5%  $\text{CO}_2$  gas for 4 to 6 days. Virus neutralization titer of a serum will be determined and calculated according to the formula of Reed-Muench method.

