### 10.4.1. Variables

The secondary endpoints include:

- (1) Observed variables from baseline at a 5- $\mu$ g and 10- $\mu$ g dose on Day 21 and 42:
  - Serum IgG titers
  - Serum neutralizing antibody titers
  - Epitope mapping (only on Day 42)

The immunogenicity parameters include serum IgG titers and neutralizing antibody titers on baseline, Day 21 and Day 42, and immune epitope mapping of EV71vac will be conducted on baseline and Day 42.

The serum IgG and neutralizing antibody titers on baseline, Day 21 and Day 42 will be summarized descriptively and the change from baseline will be tested by paired T-test or

Wilcoxon signed rank test under significance level 0.05. The results of immune epitope mapping will be summarized descriptively as well.

(2) The change in the laboratory results:

- Hematology
- Biochemistry

The analysis of laboratory includes hematology and biochemistry.

Hematology tests include CBC, such as Hb, Hct, RBC count, WBC count, WBC differential and platelet count; and biochemistry tests include ALT, AST,  $\gamma$ GT, alkaline phosphatase, total bilirubin, total protein, albumin, CPK, BUN, creatinine, uric acid, total cholesterol, triglyceride and glucose (fasting).

The descriptive summary results of laboratory for the baseline, each study visit, end of visit, the change from baseline to end of visit will be presented and paired T-test or Wilcoxon signed rank test will be used to test change from baseline under significance level 0.05.

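### Antibody titres from serial dilutions are summarised as mean change and tested by an unresolved choice of paired t-test or Wilcoxon, with no log-scale summary and no estimate of the 10 versus 5 µg contrast

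*Protocol*

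**What the plan says.** Synopsis X, item 4(4), sets the immunogenicity result: "The mean change of immunogenicity parameters include serum IgG and neutralizing antibody titers from baseline will be presented descriptively and assessing by paired T-test" or by Wilcoxon signed rank at 0.05. Item 4(2) sets the summary for every continuous variable: "continuous variables will be presented as mean, standard deviation, median and range". Section 10.4.1 has the titres "summarized descriptively and the change from baseline will be tested by paired T-test or" "Wilcoxon signed rank test under significance level 0.05". Neither place gives a rule for choosing between the tests.

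On the assays, section 7.2.2 says of the neutralisation test: "Serum specimens will be serially 2-fold diluted and added into each well of the 96-well plate", with a Reed-Muench end point. Section 7.2.1 describes a serially diluted ELISA for IgG. Section 1.3 reports the animal neutralisation titres as geometric means.

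On the design, section 3.1 says of Part II: "Subjects in this part will be randomized equally to Group A05 and Group B10". Table 6-1 gives 30 subjects per dose. Both immunogenicity objectives in section 2.2 name both doses, but no between-dose estimate is planned. Section 10.3.2 states that there is no hypothesis, and section 10.6 gives no sample size or power basis.

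**The concern.** A titre read from a dilution series is multiplicative: a rise from 8 to 32 and one from 256 to 1024 are both 4-fold. As raw differences they are 24 and 768. A mean of such differences, with its SD, is driven by the few subjects with high titres. A paired t-test on it inherits that skewness.

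Two further things follow from the wording. An open choice between two tests that can disagree on the same data can be settled after the results are seen. And a trial that randomises two doses would report two separate changes from baseline, with no estimate of what doubling the dose adds to the antibody response. That estimate could be had from the data already planned.

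**Working it through.** **Inputs from the protocol.** Table 6-1: A05 = 1 + 1 + 3 + 25 = 30; B10 = 1 + 4 + 25 = 30. The single Block A subject is assigned to A05 rather than randomised. The significance level is 0.05, taken as two-sided because sidedness is not stated. The plan has no power figure to reproduce.

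**Assumptions (not in the protocol).** Log2 titres are normal; the log2 SD of change is 1.5 and independent of baseline; the baseline log2 SD is 0.5, 1 or 2; the true rise is 2-fold or 4-fold.

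**Step 1: t-test on log titre, 2-fold rise.** The mean log2 change is 1 and its standard error is 1.5/√30 = 0.274, so the ratio is 1/0.274 = 3.65. The critical value of t on 29 df is 2.045. Power ≈ Φ(3.65 − 2.045) = Φ(1.61) ≈ 0.95; simulation gives 94%.

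**Step 2: the tests as planned, on raw change.** Raw change is 2^b × (2^c − 1), with b the log2 baseline and c the log2 change. Its spread therefore depends on the baseline spread. Simulated power for a 2-fold rise:

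| Baseline log2 SD | Paired t, raw | Paired t, log | Wilcoxon, raw |
|---|---|---|---|
| 0.5 | about 96% | 94% | 99% |
| 1 | about 91% | 94% | 98% |
| 2 | about 61% | 94% | 95% |

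For a 4-fold rise at baseline SD 2, the raw t-test has about 77% and the other two almost 100%.

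**Step 3: does the choice of test matter?** At baseline SD 2 and a 2-fold rise, the raw t-test and Wilcoxon give different verdicts in roughly 36–41% of simulated trials across repeated runs. For a 4-fold rise the figure is about 22–23%.

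**Step 4: sensitivity to baseline antibody.** A second simulation used rounded 2-fold titres with a floor of 4, seropositive baselines centred on 64, log2 SD of rise 1.5–2 and fold rise 2–8. The raw t-test had power 0.89–0.99 with no seropositives, 0.27–0.56 with 30% and 0.43–0.74 with 60%. The t-test on log titre had 0.93–1.00 and Wilcoxon 0.87–1.00.

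**Step 5: arithmetic against geometric mean.** For a log-normal titre the ratio is exp((SD × ln 2)²/2) = 1.72, 2.61 and 4.49 at log2 SD 1.5, 2 and 2.5. The top 3 of 30 subjects carry about 37% of the arithmetic mean at SD 1.5 and about 58% at SD 2.5.

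**Step 6: precision of a dose ratio.** The 95% CI factor is 2^(t × SD × √(2/30)), with t = 2.00.
- Day-42 log2 SD 1.5: 2^(2.00 × 1.5 × 0.258) = 1.71.
- Day-42 log2 SD 2.5: 2^(2.00 × 2.5 × 0.258) = 2.45.

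These SDs are linked. Baseline SD 2 with an independent change SD of 1.5 gives a Day-42 SD of √(2² + 1.5²) = 2.5 and a baseline correlation of 2/2.5 = 0.8. Adjusting for log baseline then leaves a residual SD of 2.5 × √(1 − 0.64) = 1.5, and the factor falls from 2.45 to 1.71. At Day-42 SD 1.5, correlations of 0.5 and 0.7 give 1.59 and 1.47.

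**The case against.** The strongest reply is that Wilcoxon is already in the plan and loses almost nothing. This stands: a reader might infer that the planned testing as a whole is underpowered, and the table shows that it is not. The t-test is weak only when baseline titres spread widely. With a tight baseline it matches the log analysis.

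A reader might also infer that baseline titre is never used. That is wrong, because every test is of change from baseline. Only its use as a covariate or serostatus split is missing.

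A third tempting reading is that many participants enter already primed. The background says that "more than half of children in Taiwan have no resistance to EV71", but this concerns children and the trial enrols ages 20 to 60. Exclusion (4) in section 4.2.2 bars known or potential EV71 exposure. No serology is scheduled at screening, so silent prior infection is possible, but its frequency is unknown.

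The absence of a dose comparison could be read as an error. In a phase I safety trial with no hypothesis it is an estimate left out, and group summaries still allow an informal comparison.

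Finally, a log transform, a covariate model and a rule for choosing the test may stand in a statistical analysis plan that is not shown, and the protocol does not literally say *arithmetic* or *within each dose*. That lowers the weight of the point. It does not remove it: the protocol itself names mean change, mean and SD as the result, and a later plan reporting geometric fold rise would depart from that wording.

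**Conclusion.** The point holds in limited form. The protocol fixes a mean-change summary that suits serial-dilution titres poorly, offers a t-test that can lose much power on that scale, and leaves open a choice that can decide significance. It also plans no estimate of the 10 versus 5 µg contrast.

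The size depends on titre spread, which the document does not give. For a 2-fold rise the raw t-test has from no loss (baseline log2 SD 0.5) to about 33 percentage points less power than the log-scale test (94% − 61% at SD 2). With 30 per dose, the unadjusted 95% CI for a dose GMT ratio would be about ×/÷1.7 at Day-42 log2 SD 1.5 and ×/÷2.45 at SD 2.5. The estimate is worth reporting, but not precise enough to settle small dose differences.

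This concerns a secondary endpoint and leaves the safety objective untouched. Severity: minor to moderate.

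**What to change.** Reword synopsis X item 4(4) and section 10.4.1 as follows:
- Analyse log-transformed IgG and neutralising titres.
- Report GMT by dose and visit, and geometric mean fold rise from baseline by dose at Days 21 and 42, each with 95% CI.
- Name one test in advance: the paired t-test on log titre.
- Add the 10/5 µg GMT ratio with 95% CI at Days 21 and 42, from a model of log titre on dose and log baseline titre. Label it a descriptive estimate without a hypothesis test.
- Optionally, show results by baseline serostatus, descriptively, since the share seropositive is unknown until the baseline samples are assayed.

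The cost is a wording change to a secondary endpoint and slightly more analysis. No extra subjects, visits or samples are needed.
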